**Methods:**

Patients with postprandial distress syndrome, a functional dyspepsia subtype, will be recruited at three hospitals (two in Korea and one in USA) for an international, multi-center, randomized, patient/assessor-blinded, clinical trial. The total anticipated sample size is 88. The participants will be randomly allocated into two groups: an augmented interaction group and a limited interaction group. Acupuncture, with total 12 acupoints, will be performed twice weekly for 4 weeks in both groups. Trained practitioners will provide an “augmented” or “limited” interaction context, as determined by random allocation. The primary outcome measure is the proportion of responders, the proportion of participants who answer “yes” to more than half of the adequate relief questions during the study. Secondary outcome measures include questionnaires for quality of life and symptoms of dyspepsia, and maximum tolerable volume of nutrient drink test. Data will be collected at baseline and following 4 weeks of acupuncture.

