### Outcome measurements

#### Primary outcome

##### Proportion of responder

Proportion of responder (PR) will be used to evaluate the proportion of patients who showed alleviation of FD symptoms, with relief of stomach pain or discomfort. PR is defined as the proportion of participants who answer “yes” to the adequate relief question more than half the time during the treatment period. The adequate relief question is, "After the last visit, have you had adequate relief of your stomach pain or discomfort?" The adequate relief question will be asked at every visit, starting with the second visit. PR will be calculated for the 4-week period. This indicator has been applied in several studies with functional intestinal diseases [9, 13, 14].

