### Sample size calculation

In the present study, we expected a 60% PR from the augmented group and up to a 30% PR from the limited group. These anticipated percentages were derived from previous studies [9, 14], and a consensus of experts in clinical gastroenterology. Significance was determined as α = 0.05, and a power of 1 – β = 0.80 was used. Accordingly, the required sample size in this trial was estimated according to the following formula where (p_a_ + p_l_)/2:$$ n=\frac{{\left({\mathrm{Z}}_{\upalpha /2}\sqrt{2\overline{p}\left(12\overline{p}\right)}+ Z\beta \sqrt{p_a\left(1-{p}_a\right)+{p}_l\left(1-{p}_l\right)}\right)}^2}{{\left({p}_a-{p}_l\right)}^2} $$

Assuming p_a_ = 0.6 (p_a_: the effect on the augmented group) and p_l_ = 0.3 (p_l_: the effect on the limited group), a sample size of *n* = 40 is calculated to achieve 5% significance level and 80% power. Assuming a dropout rate of 10%, a total of 88 participants were needed with a 1:1 allocation to each group (44 participants per group).

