### Statistical analysis

To compare demographic or clinical characteristics a two-sample *t*-test (in case of continuous data) or Chi-square test (in case of binary data) will be used. If a significant difference is identified between the augmented and limited groups, a general linear model-analysis of covariance will be used for continuous data, and logistic regression analysis will be used for binary data. To compare the mean value of two groups, a two-sample *t*-test will be used as a parametric method, and Mann-Whitney test will be used as a non-parametric method. The paired *t*-test will be used as parametric method and Wilcoxon signed ranks test will be used as non-parametric method to compare variables before and after intervention. The repeated measured *t*-test will be used to compare the mean value of variables between the two groups. A *P* value of <0.05 will be considered as statistical significance. Efficacy will be investigated as the difference between baseline (1 week) and the completion of treatment (4 weeks). To assess the efficacy of interventions, both intention to treat and per-protocol analysis will be performed. Participants who complete the clinical trial without any violations are targeted in per-protocol analysis. Statistical analysis other than described above will follow Guideline for Clinical Trial Statistics (Article No. 65615–13,553, December 29th 2000).

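### The analysis section names a within-subject t-test for two independent arms, contradicting its own two-sample test, and defines efficacy as a baseline-to-week-4 change that cannot apply to the primary responder outcome, to which no test is assigned

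*Protocol article*

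**What the plan says.** All four statements below are in the protocol article.

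- **Means, between groups (Statistical analysis).** One sentence assigns the two-sample t-test, with Mann-Whitney as the non-parametric option. A later sentence says that a repeated-measures t-test "will be used to compare the mean value of variables between the two groups". Between the two, the paired t-test and the Wilcoxon signed ranks test are separately given the task "to compare variables before and after intervention".
- **Efficacy (Statistical analysis).** "Efficacy will be investigated as the difference between baseline (1 week) and the completion of treatment (4 weeks"). The sentence is not limited to any class of outcome.
- **Binary data (Statistical analysis).** Chi-square appears in the sentence on demographic or clinical characteristics. Logistic regression, like analysis of covariance, is conditional on a significant difference between the groups.
- **Primary outcome (Proportion of responder).** A responder answers yes more than half the time over the treatment period. "The adequate relief question will be asked at every visit, starting with the second visit". The Sample size calculation section rests on this outcome: "we expected a 60% PR from the augmented group and up to a 30% PR from the limited group".

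**The concern.** There are two defects in what is stated.

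First, a repeated-measures t-test works on paired values from the same person. The Design section randomizes each participant 1:1 to one format or the other, so no pairs exist across the arms and the test is invalid for that comparison. An analyst following the section would hold two incompatible instructions for the same comparison.

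Second, efficacy is defined by a quantity that the primary outcome does not have. Together with the missing link between any binary test and the responder proportion, this leaves the primary analysis to be inferred. At stake is whether the test of the main hypothesis is fixed before the data are seen.

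**Working it through.** **1. Which test for means?** Set side by side, the section gives three instructions:

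| Task | Test named | Valid for independent arms? |
|---|---|---|
| Compare the means of the two groups | Two-sample t-test / Mann-Whitney | Yes |
| Compare before with after | Paired t-test / Wilcoxon signed ranks | Not a between-arm task |
| Compare means between the two groups | Repeated-measures t-test | No |

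The first and third rows are the same task with different tests. The within-subject task is already covered by the second row, so the third sentence cannot be rescued by reading it as the before/after test.

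**2. Does the efficacy definition fit each outcome?** From Table 3:

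- NDI, SF-36, STAI, VAS, PRISM and the nutrient drink test are recorded at visit 1 before treatment and at visit 8 after it. A baseline-to-week-4 change exists and can be compared between arms.
- Adequate relief is asked at visits 2, 3, 4, 5, 6, 7 and 8. That is 7 questions, none at visit 1, so more than half means 4 or more. The result is one yes/no status per participant, with no baseline value. A change from baseline does not exist.

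**3. Is a test assigned to the responder proportion?** Every named test compares means, compares before with after, is confined to demographic or clinical characteristics, or is conditional on a group difference. No sentence links one to the responder proportion.

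**4. What does the sample size assume?** The inputs, from the Sample size calculation section, are p_a = 0.6, p_l = 0.3, two-sided α = 0.05 ("Significance was determined as α = 0.05", with Z at α/2 in the formula) and power 0.80. The mean proportion is (0.6 + 0.3)/2 = 0.45. Reading the garbled term in the printed formula as 1 − p̄:

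n = [1.96 × √(2 × 0.45 × 0.55) + 0.842 × √(0.6 × 0.4 + 0.3 × 0.7)]² / (0.6 − 0.3)² = 41.97, so 42 per group.

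With unpooled variance:

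n = (1.96 + 0.842)² × (0.24 + 0.21) / 0.09 = 39.24, so 40 per group.

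The stated figure ("a sample size of *n* = 40 is calculated to achieve 5% significance level and 80% power") is therefore reproduced, exactly by the unpooled form and to within 2 per group by the printed one. Then 40 × 1.1 = 44 per group, or 88 in total. All of this is a comparison of two independent proportions. Neither a repeated-measures t-test nor a baseline-to-week-4 difference delivers that comparison.

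**5. Does naming the test change the size?** Power for 60% vs 30%:

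| Per group | Normal approximation | Chi-square, uncorrected (exact enumeration) | Fisher's exact test |
|---|---|---|---|
| 40 | 78.0% | 79.6% | 72.5% |
| 44 | 81.9% | 81.1% | 74.2% |

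The uncorrected chi-square matches the planned power closely at the planned size. Fisher's test would lose about 7 points, so the test should be named and not left open.

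**The case against.** The other side is right on several points, and they limit this one.

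- A reader might infer that the repeated-measures t-test is the only between-group test named. It is not: the two-sample t-test and Mann-Whitney stand in the same section and suit independent arms.
- A reader might infer that a baseline-to-week-4 difference cannot be used with independent arms at all. It can: change in a continuous outcome can be compared between arms with the two-sample tests named. The definition fails for the responder outcome only.
- A reader might infer that the plan contains no method able to test the primary endpoint. Chi-square and logistic regression do appear for binary data, the responder status is the only outcome defined as binary, and the sample size is built on two proportions. The intention can be guessed. The gap is that no sentence states it.
- A reader might infer that efficacy will be judged by whether each arm improves significantly on its own. The section never says so. It gives before/after and between-group comparisons separate tests.
- A reader might see two responder rules, because the abstract counts "the proportion of participants who answer “yes” to more than half of the adequate relief questions during the study" while the outcome section speaks of more than half the time in the treatment period. Both cover the same questions at visits 2 to 8, and both leave the participant who stops early equally undefined. That is a matter of missing data, commonly settled in a statistical analysis plan.

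It can also be said that the authors meant a repeated-measures analysis of variance, or that an article leaves such detail to fuller documents. The first is not what is written. With two time points, its group-by-time test would equal the two-sample t-test on change, so the sentence would add nothing. The second excuses omissions, not a stated test that is invalid or an efficacy definition that leaves out the primary outcome.

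**Conclusion.** The point holds in this form: the Statistical analysis section contradicts itself on the between-group comparison of means and names a test that is invalid for independent arms; its unrestricted efficacy definition cannot apply to the primary outcome; and no test is explicitly assigned to that outcome.

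This concerns the primary analysis, so it should be corrected before unblinding, but the correction is one of wording. Design and sample size stand. The power figures rest on the protocol's own 60% and 30%, two-sided 5%, and 40 to 44 analysed per group. No numerical bias is claimed, because the documents do not commit to an analysis that would produce one.

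**What to change.** In the Statistical analysis section:

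1. Delete the sentence on the repeated-measures t-test.
2. Limit the baseline-to-week-4 definition to the continuous secondary outcomes with a pre-treatment value in Table 3. Compare these between arms, preferably by ANCOVA on that baseline value as the standard analysis, not only when the groups are found to differ. State that paired within-arm tests are descriptive only.
3. State that the primary analysis compares responder proportions between the randomized arms by a chi-square test for two proportions, without continuity correction to match the sample size calculation (with correction the requirement would be 49 per group). Report the risk difference with its 95% CI.

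The cost is a few sentences. No new data, visits or participants are needed, because the baseline values are already collected and the total stays at 88.

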### Safety

Adverse events related to acupuncture treatment, including swelling, pain, bruising at the insertion site, discomfort, and dizziness will be assessed and recorded by Clinical Research Coordinator. Research physicians will manage adverse events, and the principle investigator will be notified. In the event of serious adverse events, the IRB and the sponsor will be notified within 24 h, regardless of causality. The principle investigator has the right terminate the study if serious adverse events occur.

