#### Acupuncture treatment

Acupuncture will be applied in the same manner in both groups. A total of 12 acupoints (Hegu [LI 4], Zusanli [ST 36], Taichong [LR 3], Quze [PC 3], Gongsun [SP 4] and Liangqiu [ST 34] bilaterally) will be used twice weekly for 4 week (8 sessions). Acupuncture will be performed as follows. The acupuncture needle will be applied to the participant’s skin. Then, after turning on the timer, the acupuncture needles will be rotated right and left for 3 s at each acupoint (total 12 acupoints). After 20 min, the timer is turned off, and the acupuncture needles will be rotated right and left for another 3 s at each acupoint, and then the acupuncture needles will be removed.

Detailed information regarding the acupuncture rationale is described in the revised STandards for Reporting Interventions in Clinical Trials of Acupuncture (STRICTA) [12] shown in Table 2.

**Table 2 Tab2:** Acupuncture treatment details based on the STRICTA (Macpherson H et al., [12]) checklist

Item	Detail
1. Acupuncture rationale	1a) Style of acupuncture - Manual acupuncture based on traditional meridian theory.
	1b) Reasoning for treatment provided, based on historical context, literature sources, and/or consensus methods, with references where appropriate - Based on the traditional meridian theory, clinical experience, and consensus by the experts in acupuncture and FD.
	1c) Extent to which treatment was varied - No additional acupoints allowed.
2. Details of needling	2a) Number of needle insertions per subject per session (mean and range where relevant) - Fixed 12 acupoints.
	2b) Names (or location if no standard name) of points used (uni/bilateral) - LI 4, ST36, LR3, PC3, SP4 and ST34 (bilateral)
	2c) Depth of insertion, based on a specified unit of measurement, or on a particular tissue level - From 5 to 30 mm.
	2d) Response sought (e.g. de qi or muscle twitch response) - ‘De qi’ sensation
	2e) Needle stimulation (e.g. manual, electrical) - Manual acupuncture
	2f) Needle retention time - Twenty minutes.
	2g) Needle type (diameter, length, and manufacturer or material) - A sterilized stainless steel needle (0.25 × 40 mm, DONGBANG ACUPUNCTURE INC., Ungcheon, Boryeong, Korea).
3. Treatment regimen	3a) Number of treatment sessions - Eight sessions.
	3b) Frequency and duration of treatment sessions - Twice weekly for 4 weeks, 20 min for each session.

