##### Maximum tolerable volume

This outcome is recorded as part of the validated nutrient drink test [26]. It is designed to induce dyspepsia, by ingesting a standard meal. When compared to a barium meal radiograph study, it is simple, non-invasive assessment that has been widely used [27, 28]. After an overnight fast, participants will consume a canned drink (Ensure, 237 ml/can, Abbott Nutrition, Columbus, Ohio, USA), at a constant rate, until they reach the maximum level of fullness. At five-minute intervals, the subjects will verbally rate their overall fullness level, on a scale of 0 to 5 (0, threshold; 5, maximum satiety). Participants will be instructed to stop drinking when their fullness level reaches 5. The actual volume consumed is the maximum tolerable volume. Questionnaires for postprandial symptoms and intensity of abdominal discomfort will be administered 30 min after drinking. If participants cannot continue to consume the test drinks, for any reason, they can voluntarily stop at any time.

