#### Participant timeline

The time schedule of enrollment, intervention, and assessments is summarized in Table 3.

**Table 3 Tab3:** The schedule of enrollment, intervention, and assessments

Study period	Screening Visit	Acupuncture treatment period							
Visit		v1	v2	v3	v4	v5	v6	v7	v8
Week		1	1	2	2	3	3	4	4
Patients									
Informed Consent	√								
Demographics	√								
Physical examination	√								
History Examination	√								
Dyspepsia History Examination	√								
Inclusion/Exclusion Criteria	√								
Serologic test/ Evaluation	√								
BDI	√								
Randomization	√								
Trial evaluation									
Investigation of Concomitant medication		√^*^	√^*^	√^*^	√^*^	√^*^	√^*^	√^*^	√^*^
Adverse events		√^*^	√^*^	√^*^	√^*^	√^*^	√^*^	√^*^	√^*^
Outcomes									
AR of abdominal pain & discomfort			√^*^	√^*^	√^*^	√^*^	√^*^	√^*^	√^*^
VAS for dyspepsia	√	√^*^							√^†^
Expectations for Relief Scale		√^*^			√^*^				√^*^
MASS		√^†^	√^†^	√^†^	√^†^	√^†^	√^†^	√^†^	√^†^
The CARE measure		√^†^							√^†^
IRI		√^†^							√^†^
NDI		√^*^							√^†^
SF-36		√^*^							√^†^
STAI		√^*^							√^†^
PRISM		√^*^							√^†^
Nutrition drink test		√^*^							√^†^
Intervention									
Acupuncture treatment		√	√	√	√	√	√	√	√

^*^, conducted before acupuncture treatment; ^†^, conducted after acupuncture treatment; BDI, Beck Depression Inventory; *AR* Adequate Relief, *VAS* Visual analog scale, *MASS* Massachusetts General Hospital Acupuncture Sensation Scale, *CARE* Consultation and Relational Empathy, *IRI* Interpersonal Reactivty Index, *NDI* Nepean Dyspepsia Index, *SF-36* Short Form 36-item Health Survey, *STAI* State-Trait Anxiety Inventory, *PRISM* Pictorial Representation of Illness and Self Measure

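### The Safety section ties the recording of non-serious adverse events to acupuncture, which both arms receive alike, while Table 3 and the serious-event rule set no such limit

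*Protocol article*

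**What the plan says.** Three places in the protocol article bear on which adverse events are recorded.

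- **Safety, first sentence:** "Adverse events related to acupuncture treatment, including swelling, pain, bruising at the insertion site, discomfort, and dizziness will be assessed and recorded", by the Clinical Research Coordinator. The reactions listed are examples, but relatedness to acupuncture qualifies the whole sentence.
- **Safety, remaining sentences:** "Research physicians will manage adverse events, and the principle investigator will be notified". For serious events, "the IRB and the sponsor will be notified within 24 h, regardless of causality".
- **Participant timeline, Table 3:** a row headed simply "Adverse events", ticked at all eight treatment visits. Every tick carries the asterisk that the footnote explains as "conducted before acupuncture treatment".

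Two further statements set the context. The Acupuncture treatment section says "Acupuncture will be applied in the same manner in both groups", while the Design section makes the augmented or limited visit the randomised factor. Of the nutrient drink test, the section on maximum tolerable volume says "It is designed to induce dyspepsia, by ingesting a standard meal". Table 3 places that test before acupuncture at v1 and after acupuncture at v8.

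**The concern.** A safety comparison between randomised arms should be able to show harm from whatever differs between them. Here that is the interaction. The limited format is deliberately impersonal and low in empathy (Table 1), so non-serious distress, or worsening symptoms after such encounters, is a conceivable arm-specific harm. Such an event is not related to acupuncture, and the first Safety sentence gives it no place in the record. The same holds for a non-serious reaction to the drink test and for progression of the underlying condition.

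The sentence also places a causal judgement ahead of the record. Discomfort is one of its listed reactions, yet at v1 the drink test and the first needling fall on the same visit and either could produce it. The coordinator who evaluates the variables is blinded to allocation (Randomization, allocation concealment, and blinding), and participants do not learn until debriefing that the interaction is under study. Neither is well placed to attribute an event to the encounter when it is reported. An event left out at that point leaves no adverse-event entry for anyone to reclassify later.

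**Working it through.** No arithmetic applies. The check sets the statements side by side.

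**1. Scope of recording**

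| Place | Events covered | Limit by cause |
|---|---|---|
| Safety, first sentence | Adverse events assessed and recorded | Related to acupuncture |
| Safety, serious-event rule | Serious events notified within 24 h | None |
| Table 3 row | Adverse events at v1 to v8 | None stated |

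The first row is narrower than the other two. The v1 check in Table 3 is marked as preceding acupuncture, so no needling has yet taken place. Under a rule confined to acupuncture-related events that check could have nothing to record. This is internal evidence that the schedule was drawn up with a wider scope in mind.

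**2. Possible sources of harm against the first sentence**

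| Source | Differs by arm by design? | Non-serious events within the first sentence? |
|---|---|---|
| Acupuncture | No | Yes |
| Augmented or limited interaction | Yes | No |
| Nutrient drink test | No | No |
| Worsening dyspepsia | Could, through the interaction | No |

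The only source inside the sentence is the one held constant. Serious events from any of the four sources are covered by the notification rule.

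**3. What the outcome measures pick up**

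- Anxiety (STAI), dyspepsia VAS, NDI and PRISM are taken at v1 and v8, with VAS also at screening. A transient episode between those visits need not show in them.
- The adequate relief question is asked at each visit from v2. A negative answer does not separate unchanged from worse.
- Questionnaires 30 min after the drink test cover symptoms and abdominal discomfort up to that time.
- Reasons for non-completion are documented (Quality control), but only for participants who leave.

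These are scores or withdrawal reasons, not dated event records with severity and relatedness. Coverage is partial.

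**4. Timing at v8**

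The v8 adverse-event check carries the asterisk (before acupuncture). The v8 drink test carries the dagger (after acupuncture). The order is therefore check, final session, drink test, and Table 3 shows no later adverse-event enquiry. Events after the v1 drink test can still be asked about at v2; events after the v8 session and drink test have no scheduled enquiry. Widening the first sentence would not by itself reach them.

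**The case against.** The strongest reply is that the article contains no exclusive rule. The Safety sentence says what will be recorded and does not say that nothing else will be. Table 3 is unqualified, the sentence on management by physicians carries no relatedness limit, and concomitant medication is reviewed at every visit. The harms one would most expect from a cold encounter, namely anxiety and worse dyspepsia, are measured in both arms. The article is also condensed, and definitions, causality procedures and e-CRF fields may be wider in the full protocol.

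Much of this stands. It shows an inconsistency of scope rather than a settled decision to discard other events, and it limits what can be said about what the trial will in fact record. It does not remove the point: the first sentence states a scope and is not merely silent, and a site that follows it literally would record less than one that follows Table 3.

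Three stronger readings are tempting and are not supported:

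- *Serious events from other causes are filtered out.* The text says the opposite: "In the event of serious adverse events, the IRB and the sponsor will be notified within 24 h, regardless of causality".
- *No event caused by the interaction can be recorded.* The unqualified Table 3 row leaves room for such events.
- *The arm comparison is uninformative by construction.* The interaction could alter reported needling discomfort, and outcome scores give some comparative information on distress and symptoms.

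Nor would counting drink tests or encounters measure the problem. Those are exposures, not missed events.

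**Conclusion.** The point holds for non-serious events. As worded, the Safety section ties their recording to the component common to both arms, in conflict with the unqualified row in Table 3 and out of step with its own all-cause rule for serious events. If the sentence is followed literally, non-serious events from the interaction, the drink test or worsening disease are not recorded as adverse events, and a tabulation by arm would miss them. The scheduled outcome measures make up for this only in part.

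The size cannot be stated in events, because the article gives no expected adverse-event rates. The conclusion assumes that the first sentence is applied as written. If the full protocol already calls for all-cause recording, what remains is a sentence in the article to correct and the missing enquiry after the v8 procedures. The change is worth making because it concerns participant safety and costs little.

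**What to change.** Reconcile the passages by rewording the first sentence of the Safety section so that every adverse event is recorded, regardless of presumed cause, at the checks already in Table 3. The listed local reactions can stay as solicited items. Assign relatedness after the event has been recorded, and tabulate all-cause events by arm alongside any tabulation of related events. How relatedness is subdivided, and who assigns it, can be left to the sponsor.

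Because the v8 check precedes the final session and the second drink test, also ask about adverse events at the post-treatment assessments already scheduled at v8, and mark this in Table 3.

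The cost is a change of wording, a relatedness entry completed after recording if the e-CRF does not already hold one, one further question at v8, and a few more non-serious entries over four weeks in 88 participants. No new visit is needed.
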